### Sample Size

To determine the necessary sample size for this study, the G*Power software was used. Based on similar studies and assuming that caregivers’ QoL is the primary outcome of this study (with all other variables treated as secondary and/or exploratory outcomes), power analysis was performed [39]. An a priori power analysis was conducted using a paired t test on the primary outcome, as an improvement in informal caregivers’ QoL was expected after the intervention. A moderate effect size (Cohen *d*=0.5), a significance level of .05, and a statistical power of 80% (1−*β*=.80) were assumed. Under these assumptions, a sample of 54 caregivers who complete the study (*df*=53) provides power greater than 80% to detect the expected effect.

Given the multiplicity of the planned analyses, confirmatory inference will be restricted to the primary outcome. Secondary and exploratory outcomes will be interpreted with caution, without applying a formal adjustment for multiple comparisons, and emphasis will be placed on effect sizes and their 95% CIs.

In addition, an attrition rate of up to 20% is anticipated (due to dropouts, absence from the postintervention assessment, or technical problems with the wearable device or platform). Therefore, we plan to recruit approximately 65 informal caregivers, so that at least 54 are expected to complete the study and be included in the primary analysis.

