#### Primary Outcome Measures

##### EQ-5D-5L

EQ-5D-5L is a self-administered scale to assess perceived health-related QoL [40-42].

Health state is obtained from the EQ-5D-5L, through its descriptive system with 5 dimensions: mobility, self-care, usual activities, pain/discomfort, and anxiety/depression. The dimensions are scored on a 5-point Likert scale reflecting the level of severity (no problem, slight problems, moderate problems, severe problems, and extreme problems or unable to perform). The health profile or health state describes the level of severity that the person perceives in each dimension and it is represented through an individual code for each dimension scored between 1 and 5 or through a single 5-digit code (ranging from 11111 to 55555).

Overall health is derived from a visual analog scale (EQ-VAS) on perceived health, from 0 to 100. In this way, the person scores his or her health on a given day, assigning it a value between 0 (the worst health you can imagine) and 100 (the best health you can imagine).

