##### Care-Related Quality of Life Instrument

Care-related quality of life (CarerQoL) is a self-administered instrument to measure care-related QoL and the impact of the care on caregivers [43].

CarerQoL will be measured through 5 negative and 2 positive dimensions (CarerQoL-7D). The 7 dimensions are fulfillment from caregiving, relational problems, mental health problems, problems with combining daily activities with care, financial issues, perceived support, and physical health problems [44]. They are scored on a Likert scale with 3 values indicating the severity level (no, some, and a lot). For negative dimensions, the values are 0 (a lot), 1 (some), and 2 (no); while for positive dimensions, the values are reversed 0 (no), 1 (some), and 2 (a lot). Score range: 0 to 14. A tariff for the CarerQoL based on Dutch preferences is also available which allows a weighted sum score, ranging from 0 to 100 [44,45]. The higher the score on the dimensions, the better the situation of care.

The CarerQoL-VAS allows rating how happy the person feels at that moment as a measure of general well-being. This construct is scored on a horizontal VAS range from 0 (completely unhappy) to 10 (completely happy). The higher the score, the better the situation in terms of well-being.

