### Analysis

The statistical analysis of the data will be performed using R software (version 4.4.3 [63]). All data will be cleaned and processed prior to analysis, and a range of statistical procedures will be performed based on the study hypotheses and objectives. The significance level for hypothesis testing is set at 5%. Numerical variables will be presented as mean and SD, along with range, minimum, and maximum values, while categorical variables will be presented as absolute frequency and valid percentage.

After performing a descriptive analysis of the variables, we will determine the distribution of the data using formal tests of normality: the Kolmogorov-Smirnov or Shapiro-Wilk tests, as appropriate. This will help decide whether parametric or nonparametric statistical methods are used. Parametric tests, such as the paired *t* test, ANOVA, and Pearson correlation, will be used to analyze data if normality is confirmed. Otherwise, nonparametric tests, including the Wilcoxon signed-rank test, Friedman and Spearman rank correlation, will be employed. Pre- and postintervention changes in the primary outcome and in the other continuous variables will be analyzed using a paired Student *t* test or, where appropriate, the Wilcoxon signed-rank test. The effect size of within-subject changes will be estimated using Cohen *d*, in order to quantify the magnitude of the observed changes. In addition, 95% CIs for these effect sizes will be reported. It is important to note that QoL, considered the primary outcome of the study, will be used for formal confirmatory inference to control the type I error rate; analyses of other outcomes will be considered secondary or exploratory.

In addition, exploratory correlation analyses will be conducted to examine relationships both among the different outcomes from the tools and between these outcomes and summary measures of the biometrical parameters recorded by the wearable devices. Depending on the distribution of the variables, Pearson or Spearman correlation coefficients will be used. For these analyses, the correlation coefficient r and its 95% CI will be reported as the primary measure of effect size. To explore relationships between categorical variables, the chi-square test will be applied. When expected cell frequencies are low, the Fisher exact test will be used instead.

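### The one confirmatory outcome, QoL, covers two instruments with four numeric scores and none is named, so the claimed type I error control does not follow from the plan

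*Protocol article*

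**What the plan says.** Two sections of the protocol article treat the primary outcome as a single thing.

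- Sample Size powers the trial with one paired t test at .05, on the assumption that caregivers' "QoL is the primary outcome of this study (with all other variables treated as secondary and/or exploratory outcomes), power analysis was performed". Because many analyses are planned, "confirmatory inference will be restricted to the primary outcome". Secondary and exploratory outcomes are to be read with caution, "without applying a formal adjustment for multiple comparisons, and emphasis will be placed on effect sizes and their 95% CIs".
- Analysis repeats the point and gives its purpose: "QoL, considered the primary outcome of the study, will be used for formal confirmatory inference to control the type I error rate". The test is a paired t test on the pre-to-post change, or Wilcoxon signed-rank where appropriate, at a 5% level.

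The section Primary Outcome Measures then lists two instruments.

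- EQ-5D-5L has a five-dimension health profile and a rating scale: "Overall health is derived from a visual analog scale (EQ-VAS) on perceived health, from 0 to 100".
- CarerQoL has seven dimensions summed to a score of 0 to 14. It also has a second scoring of the same items: "A tariff for the CarerQoL based on Dutch preferences is also available which allows a weighted sum score, ranging from 0 to 100". A separate happiness rating runs from 0 to 10: "The CarerQoL-VAS allows rating how happy the person feels at that moment".

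**The concern.** QoL is a construct. An endpoint is a particular score, compared between particular time points. Limiting confirmatory inference to one outcome controls the type I error only if that outcome leads to one test, or if the plan says how several tests are combined. Here four numeric scores have an equal claim to the label, and the only statement on adjustment concerns the other outcomes.

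This is the trial's only confirmatory claim. With the choice open, a favourable result on any one of four scores could be reported as a confirmed improvement in QoL, and a reader could not tell whether that score had been chosen in advance. The Abstract says that the article was sent in once data had been collected and ahead of analysis. A choice still open at that point could later be questioned as data-dependent.

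**Working it through.** **Inputs from the article.** Sample Size: 54 completers (df 53), d=0.5, alpha .05, one paired t test, target power 80%. Primary Outcome Measures: four numeric scores on two instruments. Results: 62 recruited. The article does not say whether the test is one- or two-sided; two-sided is assumed below. It gives no correlations between scores; those used are assumptions.

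**Step 1: the plan's own figure.** Power comes from the noncentral t distribution with df = n − 1 and noncentrality d√n = 0.5 × √54 = 3.67. This gives 95.0% two-sided (97.6% one-sided). The stated power above 80% is correct; 80% needs only 34 pairs two-sided, or 27 one-sided.

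**Step 2: error rate if any one score may count, independent scores.** The chance of at least one false positive is 1 − 0.95^k.

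- k=2: 1 − 0.9025 = 9.75%
- k=4: 1 − 0.8145 = 18.5%

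Counting only false improvements (2.5% per test), the rate is 1 − 0.975^k: 4.9% for k=2 and 9.6% for k=4.

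**Step 3: correlated scores.** Simulation with 60,000 runs, n=54, multivariate normal changes with no true effect, and two-sided t tests at 5%:

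| Assumed common correlation | Two scores, any false positive | Four scores, any false positive | Two scores, false improvement | Four scores, false improvement |
|---|---|---|---|---|
| 0.3 | 9.6% | 17.5% | 4.9% | 8.7% |
| 0.5 | 9.1% | 15.5% | 4.5% | 7.7% |
| 0.7 | 8.5% | 13.1% | 4.3% | 6.5% |
| 0.9 | 7.2% | 9.4% | 3.7% | 4.7% |

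The two CarerQoL-7D scorings use the same seven items, so a common correlation is a simplification. Setting that pair at 0.95 and all other pairs at 0, 0.3 or 0.5 gives 15.8%, 14.9% or 13.7% for four scores. These lie inside the range above.

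**Step 4: does the remedy fit the sample?** Two-sided power at d=0.5 for each score:

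| Alpha per test | 54 completers | 49 completers | Pairs needed for 80% |
|---|---|---|---|
| 0.05 (one named score) | 95.0% | 92.9% | 34 |
| 0.025 (two scores) | 91.1% | 87.8% | 41 |
| 0.0125 (four scores) | 85.7% | 81.3% | 48 |

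The column for 49 takes the 62 recruited less the anticipated 20% loss: 62 × 0.80 = 49.6, rounded down. The values at 0.025 and 0.0125 are for Bonferroni. Holm rejects whatever Bonferroni rejects and sometimes more, so its power for each score is at least as high.

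**The case against.** The strongest reply is that this is a single-arm, open-label pilot described in a condensed article. It reports effect sizes with intervals, and an unseen analysis plan, registration, ethics submission or appendix may name the score. The choice between sum and tariff is the kind of scoring detail often left to such a plan. The tariff is described only as available, so there may in effect be fewer than four candidates. This limits the size of the problem, which is why the two-score range is shown. It does not remove the problem: the article itself asserts formal confirmatory inference and error control, and even one score per instrument leaves two tests and no rule.

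The rates also assume that any one score suffices. The article states neither that rule nor its opposite. If every score had to succeed, the error rate would not exceed 5%. The rates therefore show what the wording permits, not what the investigators intend.

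Four stronger readings are tempting, and the article does not support them.

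- A reader might infer that the five-digit EQ-5D-5L code will be put through a t test. The EQ-5D-5L section also allows one code per dimension, and Analysis assigns the t test to continuous variables. The profile should not be counted as a fifth test either.
- A reader might infer that the score will be, or was, chosen with the data in hand. The Abstract dates the article's submission, not the choice of endpoint, and places it before analysis.
- A reader might infer that the trial is too small for more than one primary test. Step 4 shows otherwise.
- A reader might think the time contrast is open too. Analysis fixes it as pre to post, and Study Design and Table 1 label these t0 and t4.

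**Conclusion.** The point holds: the article claims type I error control for a single outcome, but its primary list contains two instruments and four numeric scores, with no designated score, success rule or division of alpha. The claim does not follow from the plan as written.

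If any one score could count unadjusted, the two-sided false-positive rate would be about 7% to 10% for two scores and about 9% to 17% for four, against 5%. These ranges rest on assumed correlations of 0.3 to 0.9. The figure of 18.5% requires four independent scores, which is unattainable when two of them score the same items. For false claims of improvement alone, the rates are about half as large, against a nominal 2.5%. The matter should be settled before analysis begins, because a later designation could not easily be shown to be independent of the results.

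**What to change.** Before analysis starts, name one numeric score and its change from t0 to t4 as the sole confirmatory endpoint. If that score is CarerQoL-7D, state whether it is the sum or the tariff version. Move the remaining EQ-5D-5L and CarerQoL scores to secondary.

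If both instruments must stay primary, name one numeric score from each and apply Holm at an overall 5%.

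The same designation should appear in Sample Size, Primary Outcome Measures and Analysis. If an existing document already fixes the score, cite it and give its date. The cost is a few sentences, with no change to recruitment or the sample size. The downside is that only the named score or scores can then support a confirmatory claim.

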### Outcomes and Measurements

Participants will complete the quantitative evaluations at 3 points in time: baseline (t_0_), intermediate (t_2_), and final (t_4_) through the *CuidaconTIC* platform in its evaluation section. For the final assessment, people may participate in a semistructured interview. The evaluations at these time points will be face-to-face at the reference centers or, if preferred, at the facilities of the research center.

The weekly evaluation will be performed through the *CuidaconTIC* platform and will be reminded through notifications in the mobile application.

The schedule of enrollment, interventions, and assessments, based on the proposal of the SPIRIT statement [36], can be consulted in Table 1.

**Table 1. T1:** Schedule of enrollment, interventions, and assessments.

	Enrollment	Preassessment	Intervention (3 mo)			Postassessment
	–t_1_	t_0_ (baseline)	t_1_^a^	t_2_^b^	t_3_^c^	t_4 _(post intervention)^d^
Enrollment						
Informed consent	✓					
Configuration						
Wristband delivery	✓					
*CuidaconTIC* settings	✓					
Intervention						
*CuidaconTIC* platform						
Xiaomi Band 7						
Assessments						
EQ-5D-5L		✓		✓		✓
CarerQoL^e^		✓		✓		✓
ZBI^f^		✓		✓		✓
CBI^g^		✓		✓		✓
OBQ-E^h^		✓		✓		✓
PEI^i^		✓		✓		✓
Physical activity						
Sleep						
My week-Q^j^						
Satisfaction-Q^k^						✓
SUS^l^						✓
Interview						✓

a t_1_: 6 weeks of intervention (1-6 wk).

b t_2_: mid-term assessment.

c t_3_: 6 weeks of intervention (7-12 wk).

d t_4_: 1-month post intervention.

e CarerQoL: Care-Related Quality of Life.

f ZBI: Zarit Burden Interview.

g CBI: Caregiver Strain Index.

h OBQ-E: Occupational Balance Questionnaire-Spanish version.

i PEI: Psychological Empowerment Instrument.

j My week-Q: *CuidaconTIC* weekly Questionnaire.

k Satisfaction-Q: *CuidaconTIC* Satisfaction Questionnaire.

l SUS: System Usability Scale.

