Furthermore, given the longitudinal nature of the study, data from wearable devices and scores from the weekly questionnaire will be summarized at the weekly level. For wearable data, daily recordings will be checked for validity and aggregated as weekly averages. Based on previous studies [64,65], a week will be considered valid if it contains at least 4 days with usable recordings. Trends in weekly measurements of sleep, heart rate, and step count, as well as weekly questionnaire scores, will be analyzed using repeated-measures ANOVA or the nonparametric Friedman test, depending on data distribution, including only participants who meet prespecified minimum completeness criteria for the weekly data.

To handle incomplete weekly or wearable data systematically and reduce the risk of biased estimates, the amount and pattern of missing wearable and weekly questionnaire data will be described, and all available valid weeks will be included in the analyses under a missing-at-random assumption. In addition, sensitivity analyses will be performed to assess the robustness of the longitudinal and correlational findings to different assumptions about missing data.

Regarding the qualitative analysis of the final interview, the instructions of the thematic analysis by Braun and Clarke [66] will be followed, who defined 6 phases: (1) familiarizing with the data; (2) generating initial codes; (3) searching for themes; (4) reviewing themes; (5) defining and naming themes; and (6) producing the report. The analysis will be carried out independently by 3 researchers using the previously described inductive approach, and MAXQDA 24 software [67] will be used for the triangulation of the information.

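### The two tests named for the weekly series need a complete set of weeks, so they cannot use all valid weeks as promised; the Friedman fallback also exceeds 5% if weeks are serially correlated

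*Protocol article*

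**What the plan says.** All of this is in the protocol article, under Methods.

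- **Series and tests.** The Analysis section takes "Trends in weekly measurements of sleep, heart rate, and step count, as well as weekly questionnaire scores" and says they "will be analyzed using repeated-measures ANOVA or the nonparametric Friedman test, depending on data distribution". Table 1 and its footnotes divide the intervention into weeks 1-6 and weeks 7-12, so there are 12 weekly values per caregiver. Friedman is the route when normality is not confirmed.
- **Who enters.** The same sentence ends with "including only participants who meet prespecified minimum completeness criteria for the weekly data". The content of those criteria is not given. A week counts as valid with at least 4 usable days.
- **Missing weeks.** The next paragraph says "all available valid weeks will be included in the analyses under a missing-at-random assumption" and adds sensitivity analyses for the longitudinal and correlational results.
- **Level and status.** "The significance level for hypothesis testing is set at 5" per cent. Sample Size and Analysis both restrict confirmatory inference to quality of life. Everything else is secondary or exploratory, with no formal multiplicity adjustment and with emphasis on effect sizes and confidence intervals.

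**The concern.** There are two separate problems.

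1. **The tests do not fit the missing-data promise.** Classical repeated-measures ANOVA and Friedman compare the same set of weeks within each person. They have no place for a caregiver with 11 valid weeks. That caregiver is left out or a value is imputed, and the article names no imputation. Leaving people out discards valid weeks and keeps the most adherent users. It also gives up the missing-at-random basis, because a complete-case analysis generally needs a stronger assumption.

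2. **The tests treat week order as irrelevant to correlation.** Friedman's null distribution requires the weeks to be exchangeable within a person. The ANOVA F test requires sphericity, that is, equal variances of all pairwise differences between weeks. Twelve consecutive values from one person may well be more alike when close together. If so, both tests reject too often. A Greenhouse-Geisser correction repairs the ANOVA; Friedman has no routine equivalent.

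At stake are claims of change over time in steps, sleep, heart rate and the weekly questionnaire, made from a reduced and selected group or with a p-value somewhat too small.

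**Working it through.** **Plan's own figures.** The sample size statement reproduces: a paired t test with 54 completers, d = 0.5 and a two-sided 5% level has exact power 0.950, consistent with the stated power above 80%. The article gives no error rate for the weekly tests beyond the nominal 5%. With 12 independent weeks and n = 54, simulation returns 4.95% for ANOVA and 4.96% for Friedman, so both tests behave as labelled when their conditions hold.

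**Step 1: can the promise be kept?** There are two readings of the completeness criteria.
- All 12 weeks required: the tests run, but the valid weeks of every caregiver with a gap are discarded.
- Fewer than 12 required: caregivers with gaps enter, but the named tests cannot use them without imputing or dropping weeks.

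Neither reading uses all valid weeks.

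**Step 2: how many complete sets?** Inputs: 62 recruited (Results) and 12 weeks (Table 1). The weekly validity p is assumed, since the article gives none. If weeks are independent, the expected number is 62 × p^12.

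| p (assumed) | p^12 | × 62 | whole caregivers |
|---|---|---|---|
| 0.90 | 0.282 | 17.5 | about 17 |
| 0.95 | 0.540 | 33.5 | about 33 |
| 0.98 | 0.785 | 48.7 | about 48 |

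Independence is pessimistic, because non-wear tends to cluster in the same people. At the opposite extreme, with average validity still 0.90, 10% of caregivers supply every invalid week, and 0.90 × 62 = 55.8 have complete sets. At that average the count could therefore lie anywhere from about 17 to about 55.

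**Step 3: false-positive rates with no true change.** Inputs: n = 54 (Sample Size), k = 12, 5% level. The lag-1 correlation ρ of a first-order autoregressive series is assumed.
- ANOVA: F on k−1 = 11 and (k−1)(n−1) = 11 × 53 = 583 degrees of freedom.
- Greenhouse-Geisser: both degrees of freedom multiplied by the estimate of ε = tr(M)² / [(k−1) tr(M²)], where M is the double-centred covariance matrix of the weeks.
- Friedman: Q = 12/[nk(k+1)] × ΣRⱼ² − 3n(k+1), with Rⱼ the rank sum of week j, against chi-square on 11 degrees of freedom.

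Results from 20,000 simulated trials per row (standard error at 5%: √(0.05 × 0.95 / 20,000) = 0.15 percentage points):

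| ρ (assumed) | true ε | ANOVA, uncorrected | ANOVA, Greenhouse-Geisser | Friedman |
|---|---|---|---|---|
| 0.2 | 0.94 | 5.4% | 3.9% | 5.3% |
| 0.3 | 0.87 | 5.6% | 3.7% | 5.4% |
| 0.5 | 0.67 | 8.2% | 4.6% | 7.0% |
| 0.8 | 0.37 | 11.7% | 4.9% | 9.3% |
| 0.9 | 0.29 | 13.2% | 5.1% | 10.4% |

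With n = 30, Friedman gives 5.5%, 6.5% and 9.0% at 0.3, 0.5 and 0.8, so the inflation does not depend much on how many caregivers qualify.

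A separate run of 8,000 trials (n = 54) added a person effect to the autoregressive residuals. At residual correlation 0.3, 0.5 and 0.8 it gave 6.3%, 8.0% and 11.0% for uncorrected ANOVA and 6.0%, 7.0% and 9.1% for Friedman. Greenhouse-Geisser ANOVA gave 4.1-4.4%.

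**Step 4: does a replacement hold its level?** In the same run, a t test of one least-squares slope per caregiver rejected in 4.7-4.9% of trials, including with 10% of weeks missing. The mixed model with random slope and autoregressive residuals was not simulated.

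**The case against.** The best defence has four parts.

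- **Silence on correction is not a plan to omit it.** A sphericity correction is a routine detail that a condensed article may leave to the full analysis plan. This stands: every ANOVA figure above 5% depends on no correction being applied. It does not cover Friedman, which the article itself makes the rule for non-normal data.
- **The correlation is assumed.** The documents give no week-to-week correlation, and at 0.2-0.3 the inflation is negligible. Residual values of 0.5-0.8 on top of a person effect of equal SD imply a total lag-1 correlation of (1 + 0.5)/2 = 0.75 to (1 + 0.8)/2 = 0.90, which is strong. This stands, and the size of the second problem must be stated conditionally.
- **The analyses are exploratory.** This stands and limits the consequence. A nominal 5% p-value should still be close to 5% if it is reported.
- **Completeness criteria and sensitivity analyses already deal with gaps.** This stands only in part. A threshold decides who enters but does not let a complete-block test use an incomplete record. The promise could be met for the correlation analyses, but the same paragraph also covers the longitudinal results.

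A reader might infer that the weekly tests will have a 7-12% error rate. The documents do not support that: the range needs correlations of 0.5-0.8, and its upper part needs an uncorrected F test. A reader might also infer that ANOVA requires every pair of weeks to be equally correlated. With equal variances that is sufficient for sphericity but not necessary. Nor can one infer that most caregivers will be lost, since the weekly validity and its clustering are unknown.

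**Conclusion.** The point holds as a minor one.

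The conflict between complete-block tests and the use of all valid weeks lies in the text itself and needs no assumption. An unseen analysis plan could not keep both the standard tests and the promise without adding imputation. How many caregivers it affects is unknown; 17, 33 and 48 of 62 are illustrations under independent weekly validity.

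The Friedman inflation is real but conditional: about 5-6% at an assumed correlation of 0.3, 7% at 0.5 and 9% at 0.8. ANOVA reaches about 8-12% at 0.5-0.8 only if uncorrected; with Greenhouse-Geisser it is about 4-5%.

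Only secondary or exploratory results are touched. The confirmatory quality-of-life test and its type I error are unaffected.

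**What to change.** In the Analysis section, replace repeated-measures ANOVA or Friedman for the weekly series with a method that uses every valid week and allows for serial correlation. Either will do:

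- **Simple:** fit one least-squares slope on week for each caregiver, and test the mean slope against zero, with its 95% CI.
- **Fuller:** fit a linear mixed model to all valid weeks with a random intercept, a random week slope and AR(1) residuals. Do not shorten this to a random intercept alone: in simulation a slope test from that model rejected in 13-14%, 19-20% and 35-37% of null trials at residual correlations of 0.3, 0.5 and 0.8.

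State what the completeness criteria then mean, for example the minimum number of valid weeks for a slope. If repeated-measures ANOVA is kept as a supplement, report the Greenhouse-Geisser p-value and say that it uses complete sets only. Do not base conclusions on the Friedman p-value.

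**Cost:** a change of wording and a few lines of R, with no new data. The Results section says analysis had yet to begin, so the change can be made and dated beforehand. Slope methods test linear change and can miss a rise followed by a fall, and the mixed model needs a residual check. If ANOVA is kept, the corrected version is slightly conservative when serial correlation is weak (3.7% at 0.3).

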### Intervention

The intervention lasts 3 months and is based on the use of *CuidaconTIC* and the Xiaomi Smart Band 7 activity wristband. Participants will regularly use *CuidaconTIC* services and wear the Xiaomi Smart Band 7 wristband.

*CuidaconTIC* is a technological platform for caregivers developed through the TechQoL4Carers project [34]. The research team designed and developed *CuidaconTIC* through an iterative and participatory process with informal caregivers, the platform’s end users, and other actors involved in care, such as health science professionals.

The platform is integrated into both a website and a mobile application. The services offered include a summary of the individual’s health status, training content, advice, and personalized recommendations based on their QoL, care situation, occupational balance, self-management of health, and empowerment. It also allows for synchronization with the Xiaomi Smart Band 7 activity wristband. *CuidaconTIC*, 1.0 version, will be used for the pilot project. After the trial results are integrated, the final version of the platform will be obtained. The main services of the *CuidaconTIC* platform are: My daily summary, My health, My week, I take care of myself, and I take care of you.

Caregivers are expected to access and use the TechQoL4Carers platform at least once a week to complete the weekly questionnaire and consult the training content related to self-care and care provision at least once a month.

The research team will provide caregivers with the Xiaomi Smart Band 7 wristband to capture health-related data and synchronize it with the platform. Participants are expected to use the wristband daily during the 3-month intervention. These data will be combined with other information collected through subjective measurements to provide personalized content and recommendations.

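### The weekly trend tests need complete 12-week blocks, so they cannot use all valid weeks under missing at random as the plan states

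*Protocol article*

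**What the plan says.** The relevant text is in two consecutive paragraphs of the protocol article, Methods, Analysis.

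- **Method.** Weekly sleep, heart rate, step count and questionnaire scores "will be analyzed using repeated-measures ANOVA or the nonparametric Friedman test, depending on data distribution".
- **Who is analysed.** The same sentence continues "including only participants who meet prespecified minimum completeness criteria for the weekly data".
- **What counts as a week.** For the wristband, "a week will be considered valid if it contains at least 4 days with usable recordings".
- **Missing data.** The next paragraph says that the amount and pattern of missing weekly data will be described and that "all available valid weeks will be included in the analyses under a missing-at-random assumption". It adds that "sensitivity analyses will be performed to assess the robustness of the longitudinal and correlational findings to different assumptions about missing data".

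Neither paragraph names a mixed model, another likelihood-based method or imputation.

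Under Intervention, "Participants are expected to use the wristband daily during the 3-month intervention", and the platform is to be used "at least once a week to complete the weekly questionnaire". The footnotes to Table 1 divide the intervention into weeks 1-6 and 7-12, so there are 12 repeated weeks.

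**The concern.** The named tests and the stated data rule do not fit together. Classical repeated-measures ANOVA and the Friedman test compare weeks within complete blocks, one block per participant. With 12 weeks, a single invalid week breaks the block. The rule in the next paragraph needs a method that accepts incomplete participants, and none is named.

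The missing-data assumption does not fit either. Suppose a caregiver's step count falls and, because of that, the wristband is not worn the following week. That can be missing at random, since the fall was recorded. Complete-block deletion would still remove this participant, and with them a declining trajectory. A likelihood-based model keeps the weeks seen before the gap and uses them.

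Two things are at stake. The weekly results could rest on a reduced and selected group. And with data collection finished and analysis about to start, the analyst would have to choose between two incompatible instructions with the data in hand.

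**Working it through.** The article gives no figure for the weekly analysis (no adherence rate, no expected number analysed), so there is nothing of its own to reproduce. The checks below separate the logic from the possible size.

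**1. Can any completeness criterion reconcile the two statements?**

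- If the criterion is 12 of 12 weeks, the tests run, but valid weeks from everyone else are discarded. Not all valid weeks are used.
- If the criterion is lower, some retained participants have gaps. The tests cannot use those participants without dropping them or filling the gaps.

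No threshold delivers both statements, whatever the full plan specifies.

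**2. Do the tests accept incomplete data?** One data set was simulated: 54 people (the planned completers, Sample Size), 12 weeks, each week missing with probability 0.10 independently (an assumption).

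| Analysis | Outcome | People used | Person-weeks used |
|---|---|---|---|
| Repeated-measures ANOVA, all valid weeks | stopped with an unbalanced-data error | – | – |
| Friedman, all valid weeks | returned no result | – | – |
| Complete blocks only | possible | 14 of 54 | 14 × 12 = 168 of 572 valid |
| Linear mixed model | ran | 54 of 54 | 572 of 572 valid |

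The maximum was 54 × 12 = 648 person-weeks. This run used Python routines. Other software may drop incomplete participants silently instead of stopping.

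**3. How many would have all 12 weeks?** Let p be the probability that a week is valid (assumed).

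*Independent weeks:* P(all 12 valid) = p^12.

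| p | p^12 | of 54 completers | of 62 recruited |
|---|---|---|---|
| 0.99 | 0.886 | 47.9 | 55.0 |
| 0.98 | 0.785 | 42.4 | 48.7 |
| 0.95 | 0.540 | 29.2 | 33.5 |
| 0.90 | 0.282 | 15.3 | 17.5 |
| 0.85 | 0.142 | 7.7 | 8.8 |
| 0.80 | 0.069 | 3.7 | 4.3 |

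Half are lost once p falls below 0.5^(1/12) = 0.944.

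*Missingness clustered within persons:* a beta-binomial model with mean p and intraclass correlation r. With k = (1 − r)/r, a = pk and b = (1 − p)k, P(all 12 valid) = B(a + 12, b)/B(a, b), where B is the beta function.

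| p | r = 0.1 | r = 0.3 | r = 0.5 |
|---|---|---|---|
| 0.95 | 67% | 79% | 85% |
| 0.90 | 44% | 62% | 73% |
| 0.80 | 18% | 37% | 52% |

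*From daily wear:* with a daily probability q of a usable recording and independent days, weekly validity under the 4-of-7 rule is w = P(Binomial(7, q) ≥ 4), and P(all 12 valid) = w^12.

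| q | w | w^12 |
|---|---|---|
| 0.90 | 0.997 | 97% |
| 0.85 | 0.988 | 86% |
| 0.80 | 0.967 | 67% |
| 0.75 | 0.929 | 42% |
| 0.70 | 0.874 | 20% |

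Across the scenarios discussed here the share kept runs from about 7% to 97%.

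**The case against.** **The two paragraphs can be read in sequence.** One first selects participants by completeness, then uses all valid weeks from those selected. That is a coherent reading, and the second paragraph also covers the correlation analyses, where all valid weeks can be used. The conflict is therefore better placed between the named tests and the data rule than between the two sentences. It survives, because the selected participants would still have gaps unless the criterion is 12 of 12.

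**Adherence may be good.** Entry requires a commitment to wear the wristband and regular smartphone use, the weekly questionnaire is prompted by notifications, and four usable days suffice for a valid wristband week. Against this, the Sample Size section expects up to 20% attrition, partly from technical problems with device or platform. A reader might infer that the tests will discard most participants. The documents do not support that: they give no adherence figure, and even independent weeks at 0.95 keep a majority.

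**Selection need not bias a within-person comparison.** These tests remove each participant's own level, so a difference in level between adherent and other caregivers does not by itself distort the week effect. This stands. Bias needs different trajectories, which the documents neither show nor exclude. Nor do they show that those retained would have better activity, sleep or scores.

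**Repeated-measures ANOVA can test a trend.** It can carry a linear contrast, so it would be too strong to say that the plan cannot assess trend. The article names no such contrast, and Friedman is an omnibus test.

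**The consequences are limited.** Confirmatory inference is restricted to quality of life, and sensitivity analyses on missing data are promised. Both points stand and lower the severity. Sensitivity analyses do not, however, settle what the main weekly analysis is.

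**Conclusion.** The mismatch is real: as written, the weekly analysis cannot both use the named tests in their classical form and include all valid weeks under missing at random. This follows from the text and needs no adherence assumption.

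The size of the loss is not known. The 54%, 28% and 7% figures rest on assumed weekly validity of 0.95, 0.90 and 0.80 and on independent weeks. Clustering within persons keeps more, 62% at 0.90 and 37% at 0.80 with an assumed intraclass correlation of 0.3. The defensible statement is that the tests could discard many participants.

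A reader might also treat the unstated completeness threshold as a defect. It is not one here: the article calls the criterion prespecified, and the full plan is not shown.

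The point affects secondary or exploratory results only. It should be corrected before analysis but does not threaten the trial's primary conclusion.

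**What to change.** Before analysis begins, replace both tests with one linear mixed model per weekly measure:

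- Include all valid weeks from all participants.
- Enter week as a linear term, and refit with week as a factor to check linearity.
- Use at least a random intercept per participant. Add a random slope or autocorrelated errors only if the data support them, since with about 60 people and 12 weeks they may be hard to separate.
- Report the slope per week with its 95% CI, in line with the article's emphasis on effect sizes and intervals for secondary outcomes.
- Handle skewed measures such as steps by transformation or bootstrap, not by switching to Friedman.
- Keep the participant-level completeness restriction only as a sensitivity analysis.

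The stated missing-at-random assumption then matches the method, provided the model is adequately specified. The cost is a rewritten paragraph and some model checking in R, which the plan already uses. No new data are needed.
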